#### 3.1.2. Support and triaging process

Trigger warnings and links to support will appear at relevant intervals in the survey. Survey respondents, on pressing the final submit button, will be presented with the option of asking for specific support in their own locality. To do this they have a project email set up specifically for this purpose. Emails will be triaged every 24 hours to:

the country where the individual is from, anda red/amber/green tag allocated depending on the severity of the concerns.

Appropriate, country specific services will then offer support to the individuals by making direct contact.

Post-survey submission support

At the end of the survey the participants will have a pdf of their answers, which includes the support information.

The project will be visible in sex-work spaces for approximately 18 months after the survey has finished so that there are avenues through which participants can contact us for any reasons.

The project website has a tab for support where the above information will be permanently posted until the project ends.

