#### 3.1.1. Safety and risk mitigation

Sex work is a stigmatised occupation and, as a result, many sex workers do not disclose their work. In addition, some of them are working in a criminalised context. Confidentiality, privacy and anonymity are therefore of utmost importance. This research will examine the experiences of sexual violence in sex-working populations, ¬ an issue which is sensitive and carries risk of emotional harm for everyone involved. We discuss these ethical issues below and steps we will take to mitigate the risks.

The danger of failing to hear sex worker voices accurately

This ethical dimension relates to the use and interpretation of data. There is a very real risk in research about sex work that inaccurate or misleading claims are made about a vulnerable population, which either do not seek their views or misrepresent what they say. Consequently, the overall methodological framework gives weight to the views and experiences of sex workers rather than privileging the views of other organisations such as the police and those in authority who claim to speak on behalf of sex workers. The research will adhere closely to the guidelines suggested by Jeffreys [50], as adopted by the UK Network of Sex Work Projects (UKNSWP) in 2015, which advocates for ethical, interdisciplinary scholarship which can inform grassroots activities with sex workers in communities that promote their human rights.

There are additional issues regarding ethics that are immediately evident in this project:

Potential vulnerability of participants

Sex workers are vulnerable to stigmatisation and exploitation. The normal concerns of confidentiality, anonymity and personal safety are crucial in this research, especially in ESW where sex work is partially criminalised; in Nevada where sex workers are only legal if they are working in a licensed brothel; and in Northern Ireland, where clients and other third parties are criminalised.

These sensitivities are exacerbated when we involve, as we intend to, potentially vulnerable participants who have direct and personal experiences of the matters we seek to learn about. These risks will be mitigated by the experience of the team and safeguards built into the research design as outlined below.

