Advisory Boards of experts, who have significant knowledge of working with sensitive groups and sensitive issues like sexual violence, provide oversight and advice to the research team.We will engage with groups representing sex workers, e. g. campaigners, activists and NGOs, who will participate in the development of interview and survey questions.Researchers will be employed and will receive training from the PI, RF and Co-Is on interviewing, methodological techniques, safeguarding and confidentiality.The researchers will be experienced in dealing with sensitive questioning and any fallout from discussing such issues.We will ensure that we do not interview anyone with obvious vulnerabilities, e. g. someone who is unable to give informed consent if they are under the influence of drugs or someone who is in extreme distress. Whilst there may be trains of practice which consider this exclusionary, the safety (in all aspects) of our participants is key.All participants recruited will be over the age of 18.Participants will be reminded of their right to terminate the interview at any time. If they do become upset, interviews will be stopped and only resumed with consent.Appropriate support will be provided where it is deemed appropriate. We will also calibrate how the participant is feeling and act accordingly regarding the timing and pacing of questions.We are aware that we cannot elicit information about ongoing police or legal cases since to do so could prejudice an ongoing case. We will be including in the consent documentation for both the survey and the interviews a warning to NOT discuss explicitly any current cases, names, etc, as this would then risk the information being requested by a court and could be construed as evidence. We will inform participants of this at the beginning of the interview and this information, as well as the participant’s response, will be recorded.Contact with support agencies is vital for the mitigation of harm to participants. Local drug charities, sex worker organisations and sexual violence advisory services are identified in each study site and contact information provided to participants.Anonymity: the survey will be anonymous.

Dealing with underage sex workers

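### The survey's support information is bundled in one PDF with the respondent's own answers, an avoidable exposure risk for people who conceal sex work

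*Protocol article*

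**What the plan says.** Section 3.1.2 (Support and triaging process) sets out what survey respondents receive. After submission: "At the end of the survey the participants will have a pdf of their answers, which includes the support information". One file therefore holds two things, the respondent's answers and the contacts for help.

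The same section gives other routes to help:

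- During the survey: "Trigger warnings and links to support will appear at relevant intervals in the survey".
- At submission, respondents may ask for local support: "To do this they have a project email set up specifically for this purpose".
- Afterwards: "The project website has a tab for support where the above information will be permanently posted until the project ends".

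Section 3.1.1 (Safety and risk mitigation) sets the standard against which this is read. It notes that "many sex workers do not disclose their work" and that some work in a criminalised setting, and it concludes: "Confidentiality, privacy and anonymity are therefore of utmost importance". It names breach of confidentiality among the harms the listed steps are meant to reduce. One of those steps reads: "Anonymity: the survey will be anonymous".

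Section 3.2.1 (Data storage and confidentiality) deals with data held by the team. If a personal device is used for an interview, the data must go to university storage as soon as possible and must not stay on the device. The section does not mention the copy held by a survey respondent.

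**The concern.** The two parts of the PDF need opposite handling. Support contacts are meant to be kept and reopened. A record of one's answers is something that a person who conceals sex work may prefer not to hold at all. Putting both in one file means that the take-away version of the contacts comes with the answers attached.

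The stake is personal safety and privacy. Anyone with access to the respondent's device or account could open the file and learn of the sex work and the violence reported. The study could not undo this, because the file is outside its control.

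**Working it through.** No figure lies behind this point, so the check sets the sections side by side.

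1. **Who receives the file.** The sentence in section 3.1.2 speaks of participants without exception. It does not say whether the PDF is saved automatically, sent or offered for download.

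2. **What the file would reveal.** Section 2.3.4 restricts the survey to people who have sold or exchanged sex, so a completed survey implies that history. Section 2.3 (Work Package 1) and section 2.3.6 list the content: victimisation, condom removal, non-payment, intoxication, dealings with the police, citizenship status and income.

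3. **Whether the file identifies anyone.** Section 3.1.1 calls the survey anonymous, and section 3.1.3 gives that as the reason why answers cannot be withdrawn. Nothing says that the PDF carries a name or identifier. The link to a person arises only from possession: the file sits on that person's device or account. Anonymity as described protects the study's dataset and does not extend to this copy.

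4. **Whether a described safeguard covers the copy.** The steps in section 3.1.1 concern recruitment, interviewing, consent and referral. Section 3.2.1 concerns the team's storage. Neither reaches the respondent's PDF. The device rule in section 3.2.1 applies to interview data and not to respondents, but it shows that the team regards a personal device as a poor place to leave sensitive material.

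5. **Whether the contacts can be had without the answers.** They can. The website tab carries the support information until the project ends, the survey shows links, and the project email is offered at submission. Of the routes in section 3.1.2, only the PDF is described as something the respondent takes away. The website is not a fully discreet substitute, since its address, given in section 4.1, itself names the subject.

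Steps 1 to 4 support an exposure risk that the procedure itself creates. Step 5 rules out any claim that support depends on keeping the file.

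**The case against.** The strongest reply is that this is a deliberate and reasonable choice. Respondents may want a copy of what they said. The survey was drafted with advisory boards and piloted with sex workers and NGOs (section 2.3.2), and ethics committees approved the study (section 3.1). The article is also condensed: a warning about storing the file could stand in the participant information sheet or consent documents, which are not shown. If the PDF is only offered for download, much of an opt-in already exists.

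Most of this stands as mitigation. The absence of a warning in the article cannot be counted as a defect. What remains is the stated procedure: one file holds both items, and a warning elsewhere would not separate them.

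Three stronger readings are tempting, and the documents do not support them.

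- **That discarding the PDF means losing the support contacts.** The links, email and website tab in section 3.1.2 contradict this. Section 3.1.1 adds that contact details of local services are given to participants, without saying in what form.
- **That the PDF is the court evidence the protocol fears.** The remark in section 3.1.1 that "this would then risk the information being requested by a court and could be construed as evidence" concerns explicit discussion of current cases. The same sentence says that the consent documents for both survey and interviews warn participants against this. It does not describe survey answers in general.
- **That the number of people exposed can be estimated.** The documents give no share of respondents who use shared or inspected devices, so any count would rest on a guess.

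**Conclusion.** The point holds in a narrow form. Section 3.1.2 places the support information in the same PDF as the respondent's answers, and this is the only take-away copy of it described for survey respondents. For a population that the protocol says often conceals its work, this creates an avoidable risk of exposure by possession, which sits badly with the confidentiality standard in section 3.1.1.

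The severity is low. As worded, the step applies to every respondent who completes the survey (planned n = 1,000 in section 2.3), but the number harmed cannot be derived from the documents. No endpoint, sample size or analysis is affected.

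The conclusion assumes that the PDF reaches, or can be saved to, the respondent's own device or account, and that the unseen participant documents do not already provide a separate support sheet. If they do, only the opt-in for the answers copy is left to consider.

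**What to change.** Separate the two contents. On the closing page, offer everyone a stand-alone support sheet that contains no answers and has a neutral file name. Make the PDF of answers opt-in, with a one-line warning about shared or inspected devices. Amend the sentence in section 3.1.2 to match.

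The change needs one static file and an edit to the closing page, and it leaves the questionnaire, the data and every analysis as they are. The downside is one extra step for respondents who want a copy of their answers; they can still have it.

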#### 3.1.3. Consent and withdrawal

Information is provided to potential survey respondents and interviewees through Participant Information Sheets and the study website.

Informed consent to interview will be provided by signing a consent form or giving verbal consent on the recording of the interview, depending on the relevant ethics approval in each site. All survey respondents are required to provide affirmative, free and informed consent and to confirm that they are over 18 years of age, before they can access the survey.

Interview participants can withdraw their data up to one month after their interview has been transcribed. Survey respondents cannot withdraw their data, as it is given anonymously.

### 3.2. Data management plan

#### 3.2.1. Data storage and confidentiality

Where interviews are online (Zoom, etc) we will ensure that the security of these sites for recording interviews and storage is thoroughly checked. We will move all data to the University of Strathclyde Sharepoint server for storage. All data will be transferred internationally using lawful and secure methods, in line with the appropriate General Data Protection Regulation (GDPR) [52] safeguards and policies [53] and within FAIR data principles [54].

Our data management procedures will be communicated to participants via the participant information sheet prior to interviews commencing.

We will use corporate versions of recording tools where possible–if personal devices or apps are used for the interview, data will be moved to university storage systems as soon as possible, and not retained on personal devices.

### 3.3. Advisory boards

Four Advisory Boards have been recruited to cover the individual sites: Northern Ireland; ESW, Nevada; and New Zealand. There is an Academic Advisory Board for the project which covers all sites. The Boards exist to provide a forum for discussion, feedback, oversight, guidance, meaningful involvement and independent advice to support the integrity and value of the research, following best practice [55].

Three of these Boards provide guidance in each geographical research site. Members were invited by the Research Team at the start of the study. The Boards comprise;

‘Experts by experience’ who are sex workers with lived experience;NGOs that are sex worker-led organisations and/or that work or have worked in supporting survivors of sexual violence;Academics working in the field.

The fourth Advisory Board is an Academic Advisory Committee for the study, covering all the research sites. This Board comprises internationally renowned experts who are providing specific and technical guidance and oversight for the whole study, particularly around methodology, analysis and reporting of results.

### 3.4. Status and timeline of the study

This Study is Active and currently recruiting participants as at September 2022 (Fig 1).

**Fig 1 pone.0283067.g001:**
[figure not shown]
Study timeline.

## 4. Discussion

### 4.1. Reporting

The anonymised quantitative datasets generated and analysed during this study, will be available from the: https://ukdataservice.ac.uk/ repository within three months of the end of the grant. Links to journal articles and briefings produced from the study will be available from the project website at: https://sexworkandsexualviolence.com within twelve months of the end of the grant. Where possible, outputs and reports will be available free of charge and open access.

Limitations of the study and any material difficulties encountered will be reported transparently, in order to assist future research.

### 4.2. Dissemination and impact

The Impact Plan will:

Educate policy and service delivery agencies by sharing up-to-date data on the experiences of sexual violence among sex workers.Engage practitioners, witness support, court personnel and police, sharing evidence on the experiences of sex workers in the criminal justice system, focusing on areas for improvement, continuation and change.Provide sex worker-led resources to survivors of sexual violence.Inform public debate on the issues around sex work, using our findings to dispel myths and present current trends and patterns.

We plan to engage all members of the team to write and devise the outputs as a collective approach to writing and knowledge exchange. We will write together more formal academic peer reviewed journal outputs, but will also write more accessible pieces for practitioner platforms and related conferences. We will seek out spaces where violence is a core focus (such as violence against women and girls’ strategic boards; policing authorities; government task and finish groups, etc.), to disseminate the findings more broadly, where violence against marginalised groups is being tackled. We will contribute to and host workshops / events specifically for the sex work community. We will also distribute our findings into existing organisations who work to end violence against sex workers.

### 4.3. Study limitations

There is no existing international survey of legal consciousness and/or violence against sex workers on which to build comparative results, so future replicability cannot be entirely assured. However, the transparent reporting of methods in this protocol and robust statistical tests employed should assist in future replication of this study.

Regrettably, the survey sample cannot be randomised, given the population size, sensitivity of the research and the small size of the sex working population (particularly in Northern Ireland). Online sex workers cannot be recruited simply in jurisdictions where it is illegal. Blinding of participants into different cohorts is not possible, given the lack of consistent or standard interventions on which to assess the validity of outcomes. Data are self-reported and gained through existing networks, which may result in self-selection bias from respondents and the under-representation of certain groups in results.

Inference from these data gathered in the study sites (all English-speaking, high-income countries) cannot be made to the Global South or populations of sex workers operating in other contexts.

Given the short length of the project data gathering phase, longitudinal follow-up is not possible with this cohort. The sample cannot include sex workers in prison or hospital due to ethical restrictions. It is not possible to interview people about current, ongoing legal cases so as not to risk transcripts being requested as evidence and biasing proceedings.
